## Abstract

**Background::**

Older adults commonly experience chronic medical conditions and are at risk of cognitive impairment as a result of age, chronic comorbidity, and medications prescribed to manage multiple chronic conditions. Anticholinergic medications are common treatments for chronic conditions, and have been repeatedly associated with poor cognitive outcomes, including delirium and dementia, in epidemiologic studies. However, no study has definitively evaluated the causal relationship between anticholinergics and cognition in a randomized controlled trial design. Utilizing our prior experience in deprescribing anticholinergic medications in various clinical environments, we designed an outpatient deprescribing intervention to prospectively test the potential causal relationship between anticholinergics and cognition in primary care older adults.

**Methods::**

This cluster randomized clinical trial will be conducted to evaluate the impact of an anticholinergic deprescribing intervention compared to usual care on outcomes of cognition and safety in primary care older adults. Participants will include those aged 65 years and over, receiving primary care in the greater Indianapolis area, using a strong anticholinergic within the last two weeks or with evidence of high-risk exposure in the past year. Those excluded will have a diagnosis of Alzheimer’s disease or related dementia, or serious mental illness. The trial plans to enroll 344 participants who will be cluster-randomized at the level of primary care physician to avoid contamination. Participants will complete outcome assessments every six months up to 2 years by blinded outcome assessors. The primary outcome of the study is a composite measure of cognition that includes domains assessing executive cognitive function, language, and memory. Secondary outcomes include patient-reported measures of pain intensity, depression, anxiety, sleep disturbance, and health-related quality of life.

**Discussion::**

The R2D2 trial will be the largest and longest prospective randomized trial testing the impact of an anticholinergic-specific deprescribing intervention on cognition in primary care older adults. Results could influence deprescribing methodology and provide new insight on the relationship between anticholinergics and cognition.

## Background

More than 6 million older adults annually experience disability, hospitalization, or death due to a medication-related adverse event.^1–4^ Up to 30% of older Americans use at least one strong anticholinergic medication every year.^5
6^ These medications are associated with increased risks of delirium, general cognitive impairment and Alzheimer’s disease and related disorders (ADRD),^6–16^ leading to higher morbidity, mortality, and healthcare costs.^17^

Medications with anticholinergic activity block cholinergic receptors in the brain, and have been associated with increased pathology thought to cause ADRD, with evidence from both mouse models and human studies.^18–24^ Structural changes in human brain imaging studies have also been identified among users of anticholinergics compared with non-users.^25^ Although a specific mechanism connecting anticholinergics with ADRD remains to be proven, several epidemiologic studies in humans show that anticholinergics increase the risk of ADRD among older adults receiving primary care.^7–11
13–16^ However, these association studies lack evidence for a causal relationship between anticholinergics and ADRD. This warrants the pursuit of prospective “deprescribing” trials to determine whether changing the potential risk factor (anticholinergic medication use) has an influence on cognition or important clinical outcomes related to brain health and patient safety.

Despite recommendations that anticholinergics should not be used as first line treatments in older adults, no deprescribing guidelines exist to support the safe and effective reduction of these high-risk medications. Prior studies have evaluated deprescribing interventions in reducing exposure to anticholinergics.^26–30^ These studies targeted a variety of populations and medications, including those with pre-existing ADRD, with some designed as feasibility studies with small sample sizes and short duration. However, two studies identified benefit in cognition in subgroups.^26
30^

Prior deprescribing trials suggest that pharmacist-based and educational interventions can safely deprescribe anticholinergics; however, the impact on clinical outcomes, namely performance on cognitive measures or the onset or diagnosis of ADRD, have not been tested in clinical trials.^5
26–28
31
32^ Furthermore, prior trials have not focused exclusively on strong anticholinergics, which hold the highest binding affinity to cholinergic receptors and would provide the strongest test of the link between anticholinergic medication and adverse cognitive effects.^33
34^

Therefore, we designed and initiated the randomized clinical trial, “Reducing the Risk of Dementia through Deprescribing” (R2D2) to evaluate the impact of a pharmacist-based deprescribing intervention on important cognitive and safety outcomes. The primary aim for the R2D2 trial is to determine the efficacy of anticholinergic deprescribing on objectively measured cognition compared to usual care in community-dwelling older adults. The secondary aim is to examine the quality of life and safety profile of anticholinergic deprescribing compared to usual care.

Our conceptual model (Figure 1) holds that removal of offending anticholinergic agents will lead to increased cholinergic neurotransmission and preserved or improved cognitive function including memory, executive cognitive ability, and speed of processing. The enhancement in neural function and cognitive function produced by the intervention should result in a lower risk of cognitive impairment or delay in the time to ADRD. This trial will focus on proximal outcomes with future studies planned to evaluate the impact on disease outcomes (i.e., diagnosis of ADRD).

## Methods

The R2D2 trial primary objective is to determine the efficacy of an anticholinergic deprescribing intervention on cognition compared to usual care in older adults using strong anticholinergics at baseline. The second objective is to examine the quality of life and safety profile of deprescribing compared to usual care. Third, the study intends to determine whether demographic (age, gender, race), genetic (APOE 4 status), or clinical characteristics (comorbidities, number of medications) moderate the effect of the deprescribing intervention.

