#### Inclusion Criteria:

Age 65 years and olderAt least one office visit to their primary care physician within the previous 12 monthsUse of at least one strong anticholinergic medication in the previous 2 weeks OR a ratio of total standardized days exposed within the prior 365 days of at least 0.4 or higher.^7
11
14^Original criteria required the presence of subjective cognitive dysfunction by meeting either (a) or (b) of the following criteria:
A response of “somewhat worse” or “much worse” to the SCD screening question: “In general, how would you describe your memory as compared to 10 years ago? Response offerings are: much better / somewhat better / about the same / somewhat worse / much worse. This item is derived from the Sydney Memory and Aging study^36^ and is comparable to items used to document self-report of memory in the HRS-AHEAD Study (1993 to present), the IQCODE questionnaire for cognitive decline in the elderly,^37^ and items used in the Pittsburgh cohort studies of aging.^38^A score of 5 or less on the Six-Item Screener (SIS).^39^ The SIS is a global measure of cognitive status that assesses three-item recall and orientation to year, month, and day of the week.^39^ The SIS screening test was developed in the primary care population at Eskenazi Health and validated in a racially diverse population. Scoring is determined by the number correct with a range of 0–6, where higher scores indicate better cognition; a score of ≤ 5 has a sensitivity of 97.7% and specificity of 49.3% for identifying cognitive impairment in primary care older adults.^39
40
41^Able to communicate in EnglishAccess to a telephone.

After reviewing the initial 6 months of recruitment, the study team recognized that certain eligibility requirements significantly compromised the ability to meet recruitment targets. With approval from the Data and Safety Monitoring Board (DSMB), we subsequently expanded criterion 2 to include those who achieved a calculated measure of anticholinergic medication exposure based on medical record data from the prior 12 months, and removed the requirement for criterion 4a and 4b (presence of subjective cognitive decline defined through either approach). We continued to collect data on the presence of subjective cognitive complaints in a similar manner as outlined above.

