The presence of APOE 4 alleles may modify the effect of anticholinergics on cognitive impairment, therefore, we originally planned to collect blood from each participant at baseline to include as a covariate in the responder analysis (secondary aim). However, given the COVID-19 interruption of in-person research, we revised our procedures to collect the APOE 4 variable remotely through saliva samples. Genomic DNA will be extracted from saliva samples using the DNeasy Blood & Tissue Kit (Qiagen, Inc., Valencia, CA) according to the manufacturer’s protocol. Sample kits will be distributed by mail to participant homes with instructions on how to complete and with pre-paid packaging to return to the Indiana Biobank for storage and processing. The sample kit will be distributed at the beginning of the study, but may be completed at any time of participation, and must be completed before 24 months or withdrawal from the study. Extracted DNA will be sent to LGC Limited, the preferred genotyping resource of the Indiana Alzheimer’s Disease Center and the Indiana Clinical and Translational Sciences Institute.

Because individual differences have potential to modify treatment outcomes, we will measure the following demographic and clinical factors: age, self-reported race, self-reported gender, self-reported years of education, and relevant clinical diagnoses impacting cognition such as depression, cardiovascular disease, stroke, and diabetes as we have done in prior studies.^8
17
55^ These demographic variables will be collected at baseline while diagnoses from the electronic medical record will be collected at baseline and 24 months (see Table 1). We will collect medication use through both self-report at baseline and each outcome assessment, and extract prescribed medications (medication orders) from electronic medical records prior to enrollment as well as during the 24-month study period.

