### Analysis Plan

The cluster randomized trial design will be used by randomizing primary care physicians (PCP) into the intervention or usual care arms. Outcomes will be collected and analyzed at the patient level. We will examine assigned randomization against the computer-generated randomization scheme to ensure randomization validity. Patient characteristics between the two groups will be compared using mixed effects models for continuous variables and generalized estimating equations for categorical variables while adjusting for random PCP effects. We will examine the distributions of continuous variables and use alternative approaches such as transformation or nonparametric methods in cases of violation to the normal distribution assumption. We will also examine the frequency distribution of all categorical variables and adopt exact inference procedures in cases of zero or small cell size. Any baseline variable that is found to be significantly different between the two groups will be included as a covariate in the analyses outlined below.

An intension to treat approach will be used in the analysis of all outcome measures. Composite cognitive scores collected at 6, 12, 18 and 24 months will be used as the primary outcome variables in mixed effects models. An indicator variable for intervention group (intervention vs usual care), time, interaction between group and time, and baseline cognitive scores will be included as independent variables as well as significant factors from the baseline comparison. PCP will be used as random effects to adjust for within-physician correlations. Significant group and time interaction or significant group main effect will indicate differences in cognitive function between the two groups. If significant interactions between group and time are found, post-hoc analyses will be conducted to determine the times when the two groups have significantly different cognitive scores. A significant main group effect in the absence of a group-by-time interaction would indicate differences between groups in cognitive function at all follow-up time points.

In a second set of models, we will determine whether differences between groups were accounted for by decreases in total exposure to anticholinergics from baseline to 24 months. For each medication, standardized daily exposure will be calculated using standardized daily dose as in the study by Gray^7^ and validated in our prior work^14
17

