33^ in which the daily dose is divided by the minimum effective dose. Days of standardized exposure for each medication will be the sum of the standardized days of exposure in a time period that includes each medication for each patient. This exposure is defined analogously to the pack-years concept used to characterize exposure to cigarette smoking and is a cumulative measure reflecting both exposure intensity and duration. Total exposure will be compared between the two groups using mixed effects models with group (intervention and control) as the independent variable adjusting for significant baseline variables and random PCP effects. We will then use the mixed effect model with cognitive scores at 6, 12, 18, and 24 months as outcome variables described above with total anticholinergic exposure as an additional independent variable adjusting for baseline cognitive scores and PCP random effects. Attenuation of the intervention effect from the original model would indicate that the effect of intervention is mediated through the reduction in anticholinergic exposure. Comparisons of PROMIS scores and HUI will be conducted similarly to the models we described above for cognitive scores. Exploration of potential moderation effects from *APOE*, or participants’ characteristics will be conducted by including each of these variables and its interaction with the randomization group in the mixed effects models for the outcome measures. Significant interactions will indicate significantly different intervention effects in subgroups defined by *APOE*, or participants’ characteristics.

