### Sample Size and Rationale

The sample size calculation was conducted using a mixed effects model and adjusting for the cluster randomization design. Assuming a within-subject correlation of 0.3, 0.2 and 0.1 for outcomes observed 6, 12 and 18 months apart, respectively, from the same individuals over time, 96 patients per group is required for 80% power to detect differences in composite cognitive scores of 0.6 SD at 24 months between the intervention and usual care groups with type I error rate at α=0.05 assuming linear trends in cognitive change in both groups. We further assume an intra-class coefficient (ICC) of 0.05 for primary care physicians and an average of 6 patients per physician. Accounting for the cluster design requires 120 patients per group to complete the trial. With an expected 30% attrition rate, we plan to enroll 172 patients per group into the study. Prior studies have reported mean differences in 1-year change of cognitive scores of 1.82 (SD 17) or 1.93 (SD 15) between those on definite anticholinergics versus those non-users. The effect sizes we used assume that our intervention will be able to detect a one-sixth reduction in expected cognitive decline if patients in the intervention group discontinue anticholinergics. Our assumption on the ICC is based on prior studies on prescribing patterns in physicians and practices.^58^

In Primary Aim 2, using the effective sample size of 96 patients per group accounting for the design effect from cluster randomization, we will have 85.6% power to estimate the confidence bands with half-width of 0.3 SD for the differences in symptom scores from PROMIS and HUI scores between the intervention and usual care groups during follow-up using the two-sample t-tests at the 0.05 level. Power estimates were calculated using the GLMPower and Power procedures in SAS software version 9.4 (SAS Institute, Cary, North Carolina).

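### Baseline anticholinergic exposure is not among the named moderators or fixed covariates, although the cumulative-dose hypothesis points to it and the data are collected

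*Protocol article*

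**What the plan says.** All references are to the protocol article.

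- **Methods, third objective.** The moderators are "demographic (age, gender, race), genetic (APOE 4 status), or clinical characteristics (comorbidities, number of medications) moderate the effect of the deprescribing intervention".
- **Measures.** The individual differences to be measured as possible modifiers are "age, self-reported race, self-reported gender, self-reported years of education, and relevant clinical diagnoses impacting cognition such as depression, cardiovascular disease, stroke, and diabetes". APOE 4 status is described just before them.
- **Analysis Plan, moderation.** APOE and participant characteristics are tested by "including each of these variables and its interaction with the randomization group in the mixed effects models for the outcome measures".
- **Analysis Plan, covariates.** Besides baseline cognition, a baseline variable becomes a covariate if it differs significantly between arms.
- **Analysis Plan, exposure.** A second set of models asks whether "differences between groups were accounted for by decreases in total exposure to anticholinergics from baseline to 24 months". Total exposure is compared between arms and then added to the cognitive model. "Attenuation of the intervention effect from the original model would indicate that the effect of intervention is mediated through the reduction in anticholinergic exposure".
- **Baseline data.** One eligibility route is "a ratio of total standardized days exposed within the prior 365 days of at least 0.4 or higher". The team will also "extract prescribed medications (medication orders) from electronic medical records prior to enrollment as well as during the 24-month study period". Table 1 marks self-reported and prescribed medications at baseline.

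**The concern.** The Discussion says that the intervention is meant to test whether anticholinergic drugs harm cognition. The Analysis Plan measures exposure as a cumulative quantity that combines intensity and duration. On that view, patients with more exposure at entry should on average gain more from deprescribing. Objective 3 names six other factors. The nearest of them, number of medications, counts all drugs, and the Discussion itself separates anticholinergic reduction from reducing polypharmacy in general.

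Exposure is left to a mediation model in which it is measured after randomisation. Patients who succeed in stopping a drug may differ from those who do not in ways that also affect cognition, so attenuation of the arm effect is not protected by randomisation. If total exposure to 24 months is used as worded, part of the mediator also falls after the 6-, 12- and 18-month scores that it is meant to explain.

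At stake is how well the trial can support its causal interpretation. The validity of the primary arm comparison is not in question.

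**Working it through.** **1. Is baseline exposure named?** Set side by side, the three places give:
- Objective 3: age, gender, race, APOE 4, comorbidities, number of medications.
- Measures: age, race, gender, education, diagnoses, plus APOE 4.
- Moderation analysis: APOE and participant characteristics in general.

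None names anticholinergic exposure before enrolment.

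**2. Are the data available?** Yes. The 365-day standardised ratio is an eligibility route, orders from before enrolment are extracted, and self-reported medications are taken at baseline.

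**3. What does randomisation protect?** Exposure before enrolment is fixed before any intervention, so the arm comparison at a given exposure level is a randomised one. The exposure level itself is not randomised. The interaction therefore tests whether a randomised effect varies with exposure.

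**4. The plan's own figures (Sample Size and Rationale).**
- Stated: "96 patients per group is required for 80% power to detect differences in composite cognitive scores of 0.6 SD at 24 months".
- Design effect: 1 + (6 − 1) × 0.05 = 1.25, and 96 × 1.25 = 120 completers per group.
- Attrition: 120 / (1 − 0.30) = 171.4, rounded up to 172 per group. This chain reproduces.
- The starting 96 depends on a model and test that the article does not fully specify. The forms tried give about 47 to 185 per group. I therefore take the stated 80% power at face value and work back from it.

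**5. Standard error implied by the plan.** With two-sided α = 0.05 (sidedness is not stated, so this is an assumption):

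SE = 0.6 / (1.960 + 0.842) = 0.214 SD.

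**6. Standard error of the interaction.** With 1:1 allocation and a continuous moderator scaled to SD 1 and independent of arm, the interaction per SD of exposure has about the same SE as the arm effect, 0.214. A median split doubles it to 0.428.

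**7. Power.** Power = Φ(δ / SE − 1.96). If the effect is proportional to baseline exposure, the change in effect per SD of exposure is δ = mean effect × CV. The article gives no exposure distribution, so the CV is an assumption.

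| Mean effect | CV | δ per SD | δ / 0.214 | Power |
|---|---|---|---|---|
| 0.6 SD | 0.5 | 0.300 | 1.40 | 29% |
| 0.6 SD | 0.75 | 0.450 | 2.10 | 56% |
| 0.6 SD | 1.0 | 0.600 | 2.80 | 80% |
| 0.25 SD | 0.5 | 0.125 | 0.58 | 8% |
| 0.25 SD | 1.0 | 0.250 | 1.17 | 21% |

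At CV 0.3 and a mean effect of 0.6 SD, power is 13%. With a median split, a 0.6 SD difference in effect between halves has 29% power, and 80% is reached only at 1.2 SD.

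**The case against.** **Scope.** This is a condensed article. The general reference to participant characteristics is loose enough to admit baseline exposure, and an analysis plan that is not shown may name it. That stands as a caution. However, objective 3 gives a specific list that reads as closed, and the covariate rule as stated leaves adjustment for exposure to a significance test.

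**Proxy.** Prior-year exposure is not the same as removable exposure. Eligibility is by use in the previous two weeks or by the prior-year ratio. A recent starter can have a low ratio with everything still removable, and a patient who enters on the ratio alone may have little current use. What is removed also depends on shared decisions and clinical interruption. This stands.

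**Inference.** A reader might infer that the interaction would be a randomised test of dose, or that it would separate drug removal from pharmacist contact. The article supports neither reading:
- Exposure level is not randomised and may stand in for indication or comorbidity.
- A rising gradient could reflect contact. Only one deprescribing attempt is made at a time, so patients on several anticholinergics may well see the pharmacist more.
- A flat gradient could reflect a threshold, irreversible harm in long-term users, lower deprescribing success in heavy users, or low power.

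The trial's strongest causal evidence remains the randomised arm comparison.

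**Power.** A reader who applies a one-visit test to 96 per arm gets SE = √(2/96) = 0.144 and interaction power of 55% to 99% at 0.6 SD for CV 0.5 to 1.0. That SE implies about 98.6% power for the main effect, against the stated 80%, so it is too optimistic for this plan.

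**Conclusion.** The point holds as an improvement to the analysis plan. The article names no baseline anticholinergic exposure among its moderators, does not fix it as a covariate, and analyses exposure only as a post-randomisation mediator. No stated figure is disputed.

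The gain is supporting evidence on whether the randomised effect varies with exposure, as the cumulative-dose hypothesis predicts. Power is about 29% to 80% at a mean effect of 0.6 SD and 8% to 21% at 0.25 SD. Those figures rest on the SE of 0.214 implied by the stated power, on two-sided α = 0.05, and on an effect proportional to exposure with CV 0.5 to 1.0, which the article does not give. The result should be reported as an estimate with its interval, and a null should not be taken as absence of a dose relation.

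**What to change.** 1. Include baseline standardised anticholinergic exposure over the 365 days before enrolment as a fixed covariate in the primary cognitive model, whether or not the arms differ on it.
2. Before unblinding, prespecify an exploratory interaction of arm with continuous baseline exposure, with its scale stated in advance. Report the arm difference with confidence intervals at the 25th, 50th and 75th percentiles of exposure.
3. State that this is supporting evidence and not a randomised dose comparison, that exposure may stand in for indication or contact intensity, that prior-year exposure only approximates what is removable, and that a null is not evidence of no dose relation.
4. Present it alongside the mediation model. It does not repair that model's attenuation rule, which should carry its own caveat about confounding.

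**Cost.** Analysis wording only, because the baseline medication data are already collected. The downside is one more interaction test with limited power. Data collection is expected to run to July 2026, and the change keeps its value only if it is made before unblinding.
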